#### Core programming

Participants aged 6–12 years will be offered sport plus programs emphasizing physical literacy through a range of activity options. After-school and weekend programs including ball hockey, basketball, multi-sport, soccer, dance, and rock climbing will provide a variety of sports to act as a hook and context for PYD. These programs will have a similar structure and will include dynamic fundamental movements skills, skill and game/performance content specific to the sport, and a cool down and reflection activity. Teaching of life skills will occur through role modelling, discussion, purposefully designed program activities, incentivization and recognition, and the use of teachable moments. Some programs (i.e. multi-sport, ball hockey, football, basketball) will be offered in both co-ed and girls-only formats. The priority of this age group will be the Healthy Body program pillar with the intent to develop physical literacy as PYD asset, allowing for continued engagement in physical activity and sport as youth age out of these programs and setting the stage for additional life skills development.

Participants aged 13–18 years will be offered sport plus programs emphasizing life skills development, including multi-sport, fitness, rock climbing, dance, volleyball, ball hockey, and basketball. Plus sport programs developed in collaboration with local community organizations with demonstrated histories of positive youth impact relevant to the four program pillars will also be offered, including group mentoring programs, a restorative justice program, a kitchen skills-building program, and a social circus program. School day programs for this age group will involve weekly visits by classes from local public schools, and will focus on physical literacy and nutrition education, and exposure to Science, Technology, Engineering and Math topics on-court in a sport setting. All programs will include program-specific sport and life-skill components to achieve the objectives identified for this cohort. Some programs (i.e. basketball, volleyball) will be offered in both co-ed and girls-only programming. The priority for this age group will be the Healthy Mind and Ready for School Pillars, with a secondary emphasis on Healthy Body.

Programs for the 6–12 and 13–18 year-old cohorts will be delivered in 8-week cycles with 5 cycles each year. As research participants may participate in multiple recreational programs concurrently, volume (total program hours) and duration (number of program weeks) of participation will be used as mediating variables in analyses to examine the dose-response on objectives outlined in Table 1. All programs will include life skills development using coaching strategies discussed by Camiré et al. (2011) [19], focused on 7 life skills identified in the MLSE LaunchPad Theory of Change: grit, resilience, self-esteem, self-regulation, critical thinking, social competence, and leadership.

Participants aged 19–29 years will be offered plus sport programming developed in collaboration with local community organizations offering occupational skills training and other employment services. These agencies will demonstrate strong histories of positive youth impact and will work with MLSE LaunchPad’s sport programmers to deliver integrated employment training and sport/physical activity programming. The addition of sport and physical activity is expected to offer a different context for reiteration of in-class themes (i.e. leadership and other key life skills) and to encourage increased long-term physical activity participation. The priority of this age group will be the Ready for Work pillar. Secondary emphasis will be on the Healthy Body and Healthy Mind pillars. Due to the training nature of these programs, the format will differ from the programs offered for youth aged 6–18, and programs will generally be delivered for 4 or more hours per day, 5 days per week for 8–10 weeks, with sport programming delivered in 1-h sessions 2 days/week.

#### Wrap-around services

In addition to the programs described above, participants will be offered access to mental health counselling services, nutrition programming (healthy after school snacks offered 3 days per week during program hours), and academic assistance provided through a homework club. Structured drop-in style sport plus programs incorporating life skills teaching will also be offered year-round as an additional engagement opportunity for youth who participate in registered programs, and as an alternative for youth who are unable to commit to regular registered programming.

#### Outcomes

Participants will complete a baseline assessment within 2 weeks of recruitment. Follow-up research assessments will take place at 6 months, 12 months, and 24 months from the baseline assessment with data collection concluding March 31, 2020. Outcomes have been identified based on the program theory illustrated in the MLSE LaunchPad Theory of Change (See Fig. 1). Outcomes and indicators for the primary objectives are detailed in Table 3.

**Table 3 Tab3:** Outcomes for Primary Objectives

Participants aged 6–12	
a) Increased physical literacy	Indicator:
	PLAYself Physical Literacy Assessment for Youth [36] 22-item graded self-report scale used to evaluate level of physical literacy
b) Physical activity minutes/day	Indicator:
	One-week pedometry producing at least 3 days of valid data with a minimum wear time of 10 h/day
c) Continued engagement in sport	Indicator:
	Self-report of regular sport/physical activity participation
Participants aged 12–18	
a) Life skills:	Indicator:
i. Critical Thinking ii. Resilience iii. Self-esteem iv. Self-regulation v. Social Competence vi. Grit	Critical Thinking in Everyday Life Scale [37] 20-item self-report Likert scale used to measure use of critical thinking skills including reasoning, enquiry, analysis/information processing, flexibility, and evaluation Child & Youth Resilience Measure [38] 12-item self-report scale used to measure ability to sustain well-being Rosenberg Self Esteem Scale [39] 10-item self-report Likert scale used to assess global self-esteem Motivation and Self-Regulation Subscale; derived from the School Attitudes Assessment Survey [40] 4-item self-report Likert scale used to measure ability to initiate and continue behaviours required to achieve academic goals Social Competence Scale for Teenagers [41] 9-item self-report scale used to measure positive social skills necessary to get along well with others and function constructively in groups Grit Scale [42] 8-item self-report scale used to measure stamina in dimensions of effort and interest
b) Academic Performance:	Indicator:
i. School Attendance ii. Academic Performance iii Academic Attainment	Self-report of number of missed school days over past two weeks measured as a percentage GPA as per last report card; failed courses marked as “R” on TDSB report cards will be input as 45% Self-report of highest grade/level completed
c) Physical Outcomes	Indicator:
i. Physical activity minutes/day ii. Health Behaviours iii. Continued engagement in sport	One-week pedometry producing at least 3 days of valid data with a minimum wear time of 10 h/day Healthy Behaviour Questionnaire 6-item, author-designed scale used to measure behaviours relating to sleep, nutrition, physical activity, smoking, substance use, and risky sexual behaviour Self-report of regular sport/physical activity participation
Participants aged 18–29	
a) Employment	Indicator:
i. Employment Status ii. Personal Income	Self-report of placement in job, apprenticeship or training; full- or part-time Self-report of personal income level
b) Sport Participation	Indicator:
i. Continued engagement in sport	Self-report of regular sport/physical activity participation

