## Methods/design

### Study design

The MLSE LaunchPad trial employs a single-arm, non-randomized within subject quasi-experimental design following a cohort of 350 participants aged 6–29 years old over up to 2-years of self-selected participation in programming at MLSE LaunchPad, a Sport for Development facility in downtown Toronto, ON, Canada. Data collection methods utilize repeated measures of age-specific outcomes according to hypotheses outlined in Table 1 and further described in Table 3 using self-reports and pedometer data at baseline, 6 months, 12 months, and 24 months from baseline. Qualitative assessments will take place annually throughout the data collection period using focus groups with a subset of participants. This protocol was developed in the fall of 2016 and initiated in February 2017. These data will collectively be used to evaluate the effects of intentional sport programming in a community hub on PYD and SFD outcomes in urban youth facing barriers. Moderating variables including age, gender, race, household income, postal code, program type, volume of participation and duration of participation will be explored to understand possible explanatory individual and programmatic elements of significance.

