#### Recruitment

Recruitment of participants began in February 2017 and will continue through September 2019. Participants will be followed for up to two years with data collection to conclude by March 31, 2020. During program registration and within the first week of each program cycle, new participants (and parents/guardians if applicable) will be given information about the research study and the requirements of research participation. If the participant indicates interest, they (and the parent/guardian where applicable) will be taken through the consent process.

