#### Data collection

Self-report questionnaires will be completed electronically on a personal computer, mobile phone or tablet device, or in the facility using a tablet device (Samsung Tab, iPad, or Microsoft Surface) provided by MLSE LaunchPad. Participants under the age of 8 or requiring assistance will be assisted by an adult. Participants aged 8 and over may complete questionnaires independently, but staff assistance will be offered.

Pedometer data will be collected using PiezoRx pedometers for 1 week at each research assessment time-point according to manufacturer’s instructions. Participants will be instructed on how to attach the pedometer to the waist line of clothing, to not open or tamper with the case, and to wear the device at all times unless sleeping or in water. When the pedometer is returned after 7 days, the data will be uploaded to an electronic database using minutes of activity in the Moderate to Vigorous range based on the criterion of 100 steps per minute outlined by PiezoRx.

Focus groups will be conducted annually with participants to gather personal perspectives regarding experience of programs and facility processes and impact of program involvement. Discussions will focus on: the impact of participation on health behaviours, life skills, academic engagement, job readiness and employment, and other impacts not explicitly expected or defined; the trajectory of involvement and access to programs, and wrap-around services offered in the facility.

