#### Data analysis

Preliminary analyses will be conducted after 6, 12, and 24 months of recruitment. All statistical analyses will be completed using either SPSS versions 24/25 (IBM) or *R*. Missingness in data will be evaluated for amount of missing data and patterns in missingness. Based on the results of this evaluation, a single mean value imputation method will be applied as needed.

*Ages 6–12:* Repeated measures ANOVAs will be used to examine the main effect of time on physical literacy scores, self-reported physical activity and rates of continued participation in physical activity, controlling for demographic variables such as age and gender. Moderation analyses will be used to explore the effect of program dosage in terms of the number of programs attended over the course of participation in this study on the relationship between time and change in physical literacy. A similar moderation effect will be explored in the relationship between time and the change in self-reported physical activity levels. Pearson’s product-moment correlation coefficients will also be used to explore the relationship between physical literacy and physical activity levels. A standard multiple regression controlling for age, gender, household income and housing status will be used to identify predictive variables for each of the three primary outcomes. Potential predictors for the change in physical literacy include program dosage, type of program involvement (Sport Plus or Plus Sport), physical literacy score at baseline and physical activity level. Potential predictors for the change in physical activity level and rate of continued participation in sport or physical activity include program dosage, type of program involvement, physical activity level at baseline and physical literacy score.

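### The two-week school-attendance item has no valid reading when a visit falls in the school break, and the 6-month change in physical activity is open to seasonal confounding if entry is uneven over the year

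*Protocol article*

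**What the plan says.** All references are to the protocol article.

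- **Visit timing (Outcomes):** "Follow-up research assessments will take place at 6 months, 12 months, and 24 months from the baseline assessment". The clock is each person's own baseline, not the school year.
- **Entry and end of data collection (Recruitment):** "Recruitment of participants began in February 2017 and will continue through September 2019", and "Participants will be followed for up to two years with data collection to conclude by March 31, 2020".
- **Entry points (Core programming):** programmes for ages 6-18 "will be delivered in 8-week cycles with 5 cycles each year", so participants can join at several times of year.
- **Attendance (Table 3, the adolescent cohort):** "Self-report of number of missed school days over past two weeks measured as a percentage". No rule covers a look-back that contains no school days.
- **Activity (Data collection):** "Pedometer data will be collected using PiezoRx pedometers for 1 week at each research assessment time-point".
- **Design (Study design):** the trial "employs a single-arm, non-randomized within subject quasi-experimental design". The moderators listed there include no season or calendar variable.
- **Analysis (Data analysis):** for ages 6-12, "Repeated measures ANOVAs will be used to examine the main effect of time on physical literacy scores, self-reported physical activity", adjusted for demographic variables. For ages 13-18 the time analysis lists health behaviours and six life skills, and academic outcomes enter through Pearson correlations. Missing data may be filled by single mean imputation.
- **Hypotheses (Table 1):** better school attendance is a primary hypothesis for the adolescent cohort.

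**The concern.** Two separate faults follow from running visits on each participant's own clock.

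**Attendance.** The item needs school days in the preceding fortnight. In a school break the denominator is zero. The answer is then either undefined or entered as no days missed, which cannot be told apart from perfect attendance. Spurious zeros would distort the planned correlations with academic outcomes and any test of the attendance hypothesis. If the value is set to missing instead, mean imputation could fill it with a figure drawn from other participants. This fault needs no assumption about seasonal behaviour, and because it lies in the question asked, a later analysis cannot recover the answer.

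**Activity.** One week of pedometry is a short snapshot. Month 6 sits at the opposite point of the year from baseline, while months 12 and 24 sit at the same point. With no control arm, a seasonal change and a programme effect look the same in a baseline-to-6-month comparison. Month 6 is also the follow-up that most entry months can reach.

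**Working it through.** The plan gives no figure of its own on this point, so there is none to reproduce.

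**Inputs from the article.** Entry from February 2017 to September 2019 is 32 calendar months: February to September occur three times, October to January twice. Visits are at +6, +12 and +24 months. Data collection ends on 31 March 2020.

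**Assumptions not in the article.** The break is July-August. Season in activity is a yearly cosine peaking in July with half-swing A. Entry is even over the stated months unless noted. Counts are to the month, so a visit just inside or outside the break would have a partly affected fortnight.

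**Step 1. Which visits can be reached by March 2020.**
- Month 6: all 32 entry months.
- Month 12: entry to March 2019, 26 months.
- Month 24: entry to March 2018, 14 months.

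**Step 2. Attendance look-back in the break.**
- Month 6 falls in July-August for January or February entry: 2 + 3 = 5 of 32 (16%).
- Baseline falls there for July or August entry: 3 + 3 = 6 of 32 (19%). For these entrants month 12 also falls in the break (4 of the 26 entry months that reach it), as does month 24 (2 of 14).
- Together, 11 of 32 entry months (34%) have the baseline or the 6-month look-back in the break. These are two different groups. The first loses a valid 6-month value; the second loses a valid baseline and its later season-matched visits.
- Illustration: a youth who truly misses 10% of school days and is scored 0% at such a visit shows a false 10-point difference from a term-time visit.

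**Step 3. Season in the 6-month activity change.** With season f(m) = A cos(2π(m - 7)/12) for entry month m, the false change is f(m + 6) - f(m) = -2A cos(2π(m - 7)/12).
- By entry month: January +2.00A, February +1.73A, March +1.00A, April 0, May -1.00A, June -1.73A, July -2.00A, August -1.73A, September -1.00A, October 0.
- Any full year of even entry sums to zero. The 32 months are two full years plus February-September, and that remainder sums to 1.73 + 1 + 0 - 1 - 1.73 - 2 - 1.73 - 1 = -4.73. The mean is -4.73A/32 = -0.15A.
- For the 14 entry months that reach month 24 (one full year plus February and March), the mean is +2.73A/14 = +0.20A. For the 26 that reach month 12 it is +2.73A/26 = +0.11A.
- If A were 5 to 10 min/day (assumed), the range -0.15A to +0.20A is -0.75 to +1.0 min/day at A = 5, and -1.5 to +2.0 at A = 10.
- Variance remains even when the mean cancels: over a full year the SD of the false change is 2A/√2 = 1.4A, or 7 to 14 min/day on the same assumption.
- At months 12 and 24, f(m + 12) - f(m) = 0 and f(m + 24) - f(m) = 0.
- Of the 32 entry months, 16 give a winter/summer pair and 16 a spring/autumn pair, where the difference may be much smaller.

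**Step 4. What a net shift would do.** Let s be the net seasonal shift in SDs of change. With no true effect, the two-sided 5% rejection rate of the 6-month contrast is 1 - Φ(1.96 - s√n) + Φ(-1.96 - s√n).

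| s | n = 100 | n = 150 |
|---|---|---|
| 0 | 5% | 5% |
| 0.05 | 8% | 9% |
| 0.1 | 17% | 23% |
| 0.2 | 52% | 69% |

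The article gives neither the seasonal size nor the entry distribution, so which row applies is unknown.

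**The case against.** A reader might infer that the whole time effect on activity and attendance is largely a calendar effect. The article does not support that, for these reasons.

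- **The activity bias is conditional.** The shifts of +1.73A and -2A belong to single entry months. A time effect averages over participants, and even entry brings the mean close to zero. This stands. Even entry is not assured, because recruitment takes place at registration and in the first week of programme cycles, but nothing shows that it is uneven.
- **The long-term contrasts are protected.** Months 12 and 24 match the baseline season, the stated interest is long-term participation, and no section singles out the 6-month contrast as primary. This stands for activity. It does not rescue attendance for July-August entrants, whose matched visits all lie in the break.
- **Attendance is not in the listed time analyses.** The Data analysis section names only correlations for it. A time-effect test rests on the hypothesis in Table 1 and a general sentence in the Background about age-specific outcomes. This stands and limits the claim to those uses.
- **The activity variable differs.** The ages 6-12 analysis names self-reported activity while Table 3 specifies pedometry, so figures in min/day apply only to the latter. Self-reported regular sport participation has no one-week window, and no seasonal effect on it is claimed here.
- **A covariate may sit in a document not shown.** The covariate list is open-ended, so this is possible for the calendar term. It does not answer the attendance point, because the look-back is fixed in Table 3 itself.
- **Camps are programming.** Full-day camps are part of the intervention in Table 2. If they run in summer, a summer term could remove a real effect. This stands and is carried into the fix.

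**Conclusion.** The point holds in two parts of unequal strength.

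**Firm:** the attendance item as worded gives no valid value in a school break. On an assumed July-August break and even entry, this affects the 6-month visit for 5 of 32 entry months, and the baseline with any 12- and 24-month visits for another 6 of 32.

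**Conditional:** the 6-month change in activity cannot be separated from season within a person, and nothing named in the article absorbs it. The mean bias depends on how uneven entry is. Under even entry it is about -0.15A to +0.20A on the assumed cosine, and the main cost is added variance. Its direction and size in this study cannot be known from the article. The article gives no ground for moving the primary contrast away from the 6-month visit, which is the best-populated follow-up.

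**What to change.** 1. **Table 3, attendance.** Define the look-back as the last two weeks in which school was in session. Treat responses already collected in a school break under the present wording as missing: not as full attendance, and not mean-imputed.
2. **Data analysis, activity outcomes.** Add the calendar month of each assessment, or a school-term/summer indicator, as a time-varying covariate, using a mixed model if repeated measures ANOVA cannot take it. Keep all visits and report the season-matched baseline-to-12-month contrast alongside the 6-month one.

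**Cost.** One reworded item and a slightly different model, which needs the date of each assessment. Recruitment began in February 2017, so later attendance responses lose some comparability with earlier ones. A summer term may absorb some real effect of camp programming, so results should be shown with and without it.

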### Study population

#### Inclusion criteria

Participants will be eligible for the study given the following criteria upon enrolment for the study:
Age 6–29 yearsRegistered member of MLSE LaunchPadAttending programming at MLSE LaunchPadAbility to speak, understand and read EnglishPhysically able to participate in programming with or without the use of assistive devices-Recruited within 8 weeks of commencing program participation.

MLSE LaunchPad defines ‘youth facing barriers’ as ‘youth who may need greater supports and services to reach their full potential’, including low income, racialized, Indigenous, new to Canada, LGBTQ2S, and homeless or underhoused youth; youth in care or leaving care; and youth in conflict with the law. Demographic data will be collected in self-report surveys and through member registration and used to define characteristics of the population. No formal process is used to ensure youth accessing MLSE LaunchPad’s programs meet the stated criteria for ‘youth facing barriers’, and no youth are excluded from programming based on these criteria; however, the neighborhood demographics and outreach strategy have to date resulted in program participation by youth who meet the criteria outlined.

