#### Intervention

Programs (described in Table 2) include a mix of sport plus programs, developed by an in-house team of sport programmers, and plus sport programs, several of which have been developed collaboratively with community partner organizations with similar target demographics and intended PYD impacts. The collaborative programming model engages the expertise of the aforementioned community partner organizations; academic partners with knowledge of PYD and SFD; and partners in the broader sport and physical education sectors. Each program falls under one of the following program pillars: Healthy Mind, Healthy Body, Ready for School, or Ready for Work. All programs incorporate sport and physical activity as a part of a psychologically and physically safe learning environment. An evidence-based coaching philosophy creates consistent coaching standards across programs, ensuring that life skills teaching is explicitly incorporated into all programs and that peer-peer and peer-leader relationships are emphasized. Coaches delivering programs are trained in life skills development and transference and physical literacy and fundamental movement skills by academic partners to provide high-quality, evidence-based and intentionally designed youth SFD programming based on the program theory explicated in the MLSE LaunchPad Theory of Change (see Fig. 1). Youth mentors, who are present in the facility before, during and after program times, act as resources to participants and facilitate connections with peers, leaders, and community resources. Youth mentors play a key role in the teaching of life skills by modelling positive behaviours and using teachable moments and are considered a key element of programming for all 3 age groups.

**Table 2 Tab2:** Program Descriptions

Age	Available Programming	Expected Outcomes	Evaluation Tool

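### The continued-sport outcome does not separate LaunchPad sessions from sport elsewhere, so its planned association with program dose can arise from attendance alone

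*Protocol article*

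**What the plan says.** **Outcome.** In Table 3 (Outcomes section) the indicator for continued engagement in sport is "Self-report of regular sport/physical activity participation", identical for all three cohorts. The article does not say what counts as regular, or whether sessions at the facility count.

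**Intervention.** The Intervention section says: "All programs incorporate sport and physical activity as a part of a psychologically and physically safe learning environment".

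**Intended construct.** For ages 6–12, Core programming describes physical literacy as an asset "allowing for continued engagement in physical activity and sport as youth age out of these programs". For ages 19–29 the same section expects the sport component to raise physical activity in the long term.

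**Dose analyses.** For ages 6–12 the Data analysis section says: "Potential predictors for the change in physical activity level and rate of continued participation in sport or physical activity include program dosage". For ages 13–18, a set of predictors that includes dosage is used for continued participation. For ages 19–29 the dosage regression is on employment, not sport. The secondary hypothesis in Table 1 expects volume and duration of participation to correlate positively with the primary outcomes of every cohort.

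**Neighbouring outcomes.** Physical activity at ages 6–18 is "One-week pedometry producing at least 3 days of valid data with a minimum wear time of 10 h/day", with participants told "to wear the device at all times unless sleeping or in water". Employment status at ages 19–29 is "Self-report of placement in job, apprenticeship or training; full- or part-time".

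**Timing.** Participants must already be attending at entry and be "Recruited within 8 weeks of commencing program participation". Baseline follows within 2 weeks of recruitment, and follow-up is at 6, 12 and 24 months from baseline.

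**The concern.** The intervention is sport and the outcome is doing sport. A youth enrolled in a weekly program at follow-up can truthfully report regular participation because of that program alone. A participant whose sport will outlast the program and one who is simply still in it then give the same answer.

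The dose models suffer most. Youth with more accumulated program exposure are more likely to be attending still at an assessment, and attending is enough to satisfy the outcome. Attendance therefore enters both the predictor and the response. The points scheme under Incentivization rewards attendance and so can move both together. A dose–response found this way could be reported as evidence that the program builds lasting sport habits when it shows only that attenders attend. If the split between inside and outside sport is never asked, later analysis cannot recover it.

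**Working it through.** The plan states no figure for this outcome; its power figure for ages 6–12 concerns physical literacy. The check is therefore a short derivation, a simulation with no carry-over, and a timeline.

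**1. What the indicator measures with no carry-over.** Let *p* be the proportion doing regular sport elsewhere, unrelated to the program, and *a* the proportion still attending. Assume every attender answers yes.

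- P(yes | attending) = 1 and P(yes | not attending) = *p*, a gap of 1 − *p*.
- For assumed *p* of 30%, 50% and 70%, the gap is 70, 50 and 30 percentage points.
- Overall P(yes) = *a* + (1 − *a*)*p*. With *p* = 40% and *a* = 50%: 0.50 + 0.50 × 0.40 = 70%.

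**2. What this does to the dose association.** Inputs:

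- n = 150, the planned size of the 6–12 cohort (Sample size section).
- Sport elsewhere at 30%, 50% or 70%, independent of dose (assumed).
- Attendance at follow-up of 30%, 50% or 70% at average dose, with log-odds rising by 1 per SD of dose (assumed).
- Two-sided test at 0.05 of the correlation between dose and follow-up status, without covariates.

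| Sport elsewhere | Mean correlation | Share significant |
|---|---|---|
| 30% | 0.26–0.31 | 90–98% |
| 50% | 0.20–0.25 | 68–88% |
| 70% | 0.14–0.19 | 37–64% |

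Ranges are over the three attendance levels. When the outcome counts only sport elsewhere, 5% of simulated studies are significant, the nominal rate. The 13–18 cohort is planned at 100, so the same correlation would reach significance less often there.

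**3. Change over time.** Baseline falls at most 8 + 2 = 10 weeks after program start, in youth who are attending.

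- If program sessions count at baseline too, baseline is near 100%. In the example above, change is 70 − 100 = −30 points; across the simulated grid it is about −10 to −47.
- If baseline answers leave the program out, baseline is 40% and change is 70 − 40 = +30 points; across the grid it is about +10 to +47.

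Change depends on attendance in both cases, but its sign depends on how the item is understood at entry.

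**4. Pedometry.** One weekly 60-minute session (Learn to Play, Table 2) adds at most 60/7 = 8.6 min/day over seven valid days, or 60/3 = 20 min/day if only three days are valid and include it. If 30–50% of the session is moderate-to-vigorous (assumed), this is 2.6–4.3 or 6–10 min/day. The twice-weekly 2-hour program for ages 6–12 totals 240 minutes: at most 240/7 = 34.3 min/day, or 10.3–17.1 at the same shares.

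**5. Training placement.** Partner courses last 8–10 weeks (Core programming). The first follow-up is about 26 weeks after baseline, so a course under way at entry has normally ended by then. Overlap is likelier at baseline.

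**The case against.** The strongest reply is that participation itself is a legitimate target. The Background defines sport plus programs by their aim of getting more youth into sport, and Table 2 lists increased or continued participation as an expected outcome at ages 13–18. Staying in a free sport program counts towards that. This stands, and it is why total participation should still be reported. It does not rescue the dose models or any claim about sport after the program, which need the two sources kept apart.

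Second, dosage accumulates over the study while the outcome is status at an assessment, so the two are not the same quantity. That is correct. The overlap is partial, and the simulation treats it so, with dose only raising the odds of still attending.

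Third, Table 3 condenses the instrument, and the actual item may already exclude LaunchPad sessions. This cannot be settled from the article and lowers confidence. If the item does so, Table 3 needs only to say it.

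Three stronger readings are tempting, and the documents do not support them:

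- A reader might infer that the time effect is inflated. Participants already attend at baseline, so a ceiling or a decline is equally possible.
- A reader might infer that trainees meet the placement outcome by definition at follow-up. The courses normally end before the 6-month visit, and counting them at baseline would work against showing an increase.
- A reader might infer that pedometer minutes are invalid because they include sessions. The hypothesis is increased physical activity, and program minutes are real activity. Only reading a dose relation as change beyond sessions would be wrong.

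**Conclusion.** The point holds for continued engagement in sport. As printed, the indicator cannot distinguish carry-over from continued attendance, and the plan relates it to dosage by regression at ages 6–12 and 13–18 and by hypothesis in all cohorts. With no carry-over at all, a dose correlation of about 0.14–0.31 is plausible, significant in about 37–98% of studies of 150. These sizes rest on the assumed rates of outside sport and attendance, the assumed link between dose and attendance, and attenders answering yes because they attend. Change over time also partly tracks attendance, in a direction the documents leave open. Pedometry is a lesser matter of interpretation, and training placement is an ambiguity to settle. Confidence is moderate, because the questionnaire wording is not shown.

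**What to change.** - **Sport participation.** At each assessment record regular sport at LaunchPad and outside LaunchPad as separate items, and define regular. Use outside participation as the outcome in the dose and predictor models and for any claim of engagement beyond the program. Report total participation alongside.
- **Pedometry.** Keep all-day minutes as the physical activity outcome. For dose questions add a supportive analysis on non-program days, flagged from the centrally collected attendance data. Limit it to programs where attendance is logged; Open Gym is unregistered, and the article does not show that every visit is captured.
- **Placement.** State whether enrolment in a LaunchPad partner training course counts as placement, and apply the same rule at baseline and follow-up.
- **If the item already excludes LaunchPad sessions,** say so in Table 3.

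The cost is one extra questionnaire item and a linkage to attendance records. Recruitment began in February 2017, so anyone already enrolled would have no baseline split; for them the outside item supports analysis of follow-up status but not of change. The supportive pedometer analysis will have fewer valid days, and outside-only rates will look less favourable than total rates.
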